## Methods

2

The study protocol is designed and performed according to the principles of the Declaration of Helsinki and in line with the guidelines of the clinical trial committee for PMOP. The Consolidated Standards of Reporting Trials (CONSORT) statement^1^ has been used to develop the study methodology. This study’s Clinical Trial Registration Number is (ChiCTR2300073863) and has been registered at http://www.chictr.org.cn. The protocol of this study was approved by the Ethics Committee of Bao’an Hospital of Traditional Chinese Medicine, Shenzhen (KY-2023-001-30).

### Design and study setting

2.1

A total of 96 participants meeting the diagnostic criteria for PMOP according to the guidelines of the clinical trial committee will be recruited at Bao’an Hospital of Traditional Chinese Medicine. Subjects will be informed of every study detail and sign an informed consent form.

This randomized, controlled clinical trial comprises three parallel groups. It compares the effectiveness of the individualized CEA group, CEA combined with the rTMS group and rTMS groups (Figure 1).

**Figure 1 fig1:**
[figure not shown]
Flow chart.

### Participants recruitment

2.2

Three ways of recruiting participants will be used: firstly, we intend to recruit the participants from the clinics of Shenzhen Bao’an Hospital of Traditional Chinese Medicine. A workshop will be convened to formulate how to collect participants. In addition, posters will be placed outside the clinic to attract potential candidates. Secondly, Another is recruiting through radio, television, newspapers, etc. In these advertisements, we will introduce the target population briefly and offer free screening and treatment to suitable participants. Thirdly, we will conduct educational talks and offer clinic services to postmenopausal women with OP. By disseminating basic knowledge, we may attract appropriate subjects.

### Inclusion criteria

2.3

Patients who meet the Chinese and Western diagnostic criteria for PMOP. Western medical diagnostic criteria: Referring to the Clinical Practice Manual-Osteoporosis and Bone Mineral Disorders and the Primary Osteoporosis Primary Care Guidelines (2019) from the Chinese Medical Association, as well as the one formulated by American College of Clinical Endocrinologists (AACE) associated with the American College of Endocrinology (ACE) named as the 2020 AACE/ ACE Clinical Practice Guidelines: Diagnosis and Treatment of Postmenopausal Osteoporosis and the World Health Organization (WHO) diagnostic criteria for osteoporosis based on Dual-emission X-ray Absorptiometry (DXA) measurement. The diagnostic criteria for TCM identification are mainly formulated regarding the Guidelines for the Diagnosis and Treatment of postmenopausal osteoporosis (bone impotence) in Chinese Medicine (2019 edition). The Chinese medicine identification criteria is adopted from the Guidelines for Clinical Research on New Chinese Medicines on Kidney Deficiency formulated by the Ministry of Health of China in 2002.Patients with right-handedness; junior secondary school education or above.Age 45–70 years old female with natural menopause for over 2 years.Those who have good compliance and understanding voluntarily join the project and agree to sign the informed consent form.

### Exclusion criteria

2.4

Patients with diseases that do not fall into the category of PMOP or even primary OP, such as other conditions affecting bone metabolism: endocrine disorders (gonadal, adrenal, parathyroid, and thyroid diseases, etc.), immune diseases such as rheumatoid arthritis, gastrointestinal and renal diseases affecting the absorption and regulation of calcium and vitamin D, malignant conditions such as multiple myeloma, long-term use of glucocorticoids or other drugs affecting bone metabolism, various congenital and acquired abnormalities of bone metabolism, etc.;Patients with malignant neoplasms, primary severe diseases of the cardiovascular, cerebrovascular, hepatic, renal, and hematopoietic systems, or either severe skin diseases or psychiatric disorders who are unable to cooperate or adhere to the completion of treatment;Patients who have accepted anti-OP medication (excluding primary therapy) within the previous 6 months or who have been on the long-term and sustained use of drugs that may affect bone calcium metabolism;Patients who have used psychiatric drugs such as antidepressants or anti-anxiety drugs in the past 6 months;Those with structural abnormalities of the brain, such as occupying intracranial lesions, brain malformations, severe strokes (affecting brain structure), etc.;Those with treatment contraindications such as allergy to CEA;Those with contraindications to rTMS treatment: e.g., with aneurysm clips, implanted neurostimulators, pacemakers, automatic defibrillators, cochlear implants (electrodes) or visual foreign bodies, head-mounted with metal materials, etc.;Those with a history of alcohol, drugs, or other kind of substance abuse or dependence within 1 year;Those with creatinine clearance <35 mL/min;Those who are unable to adhere to the treatment.

### Drop-out and exclusion criteria

2.5

For those who did not complete the trial within 12 weeks±5 days, categorization will be made according to the reason for not completing the trial.

#### Drop-out

2.5.1

Including patient self-withdrawal due to poor efficacy, intolerance, refusal to account, loss to follow-up, and doctor dissuasion due to poor adherence, comorbidities, specialties, adverse reactions, etc.

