#### Exclusion criteria

2.5.2

a Those who do not meet the inclusion criteria and are mistakenly included;

b Subjects with poor adherence, not following the designed treatment regimen strictly, or whose something would affect the observed results of the study during the trial;

c Subjects with incomplete information on various materials.

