#### Discontinuation criteria

2.5.4

a Subjects who have experienced a severe adverse reaction or event that prevents them from continuing to be under treatment;

b Subjects who develop severe comorbidity or other systemic serious medical conditions during the trial and are unable to persist;

c Subjects who have poor compliance and do not cooperate with the relevant treatment despite repeated explanations;

d Subjects who request to withdraw from the study on their own;

e Subjects who take other drugs privately during the treatment period, which may interfere with the study results;

f The patient lost during the follow-up period for various reasons.

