### Blinding

2.7

A professional acupuncturist will independently operate the participants in the CEA group, while an independent professional physician is tasked with treating the rTMS group. The patients in the combined treatment group are to be treated by two trained physicians who collaborate to complete the two intervention plans. The treatment therapists of each group could not obtain specific treatment modes for the other two groups. Upon completing the treatments for the three groups, they are to inform the evaluator of the group code corresponding to the participant. The evaluator is to conduct scale testing on the participants and collect and record data in the case report forms, without access to information about the patients’ group allocations. The researchers responsible for statistical calculations are to remain blinded to the group allocations, having access only to the group codes.

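### Section 2.5.2 b and c exclude enrolled women for poor adherence or incomplete information and nothing keeps their data, so both DXA-based primary comparisons can depend on what happens after randomisation

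*Protocol article*

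**What the plan says.** Section 2.5 of the protocol article deals with women who do not complete the trial within 12 weeks (plus or minus 5 days). For them, "categorization will be made according to the reason for not completing the trial". Three lists follow that bear on this point.

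- **2.5.2, exclusion.** Item a concerns women enrolled by mistake, so the list applies to women already in the trial; eligibility exclusions are in 2.4. Item b begins "Subjects with poor adherence, not following the designed treatment regimen strictly" and goes on to an open clause covering anything that could influence the observed results. Item c is "Subjects with incomplete information on various materials".
- **2.5.1, drop-out.** One class holds self-withdrawal for poor efficacy or intolerance, loss to follow-up, and "doctor dissuasion due to poor adherence, comorbidities, specialties, adverse reactions, etc".
- **2.5.4, discontinuation.** One list holds reasons that concern treatment: "Subjects who have experienced a severe adverse reaction or event that prevents them from continuing to be under treatment" (a), severe comorbidity (b), "Subjects who have poor compliance and do not cooperate with the relevant treatment despite repeated explanations" (c) and "Subjects who take other drugs privately during the treatment period, which may interfere with the study results" (e). It also holds withdrawal from the study (d) and loss to follow-up (f).

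DXA is done at weeks 0 and 12 only (2.10.1 and Table 1). In 2.10.2 both positive response categories require the bone density result. Section 2.12 lists retention measures and a case tracking system. Section 2.14 names the tests and the Bonferroni correction but says nothing about which participants are analysed.

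**The concern.** Randomisation makes the arms comparable only if the women compared are those who were randomised. Adherence and completeness of records are mostly observed afterwards; Table 1 assesses compliance up to week 12. A woman who responds poorly or reacts badly is more likely to miss sessions or take another drug, so the exclusion reasons may be related to outcome.

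They may also be related to arm. The treatment load differs threefold to fourfold between CEA and the other two arms. Staff also know which treatment they give: under 2.7, "A professional acupuncturist will independently operate the participants in the CEA group", a separate physician treats the rTMS arm, and the two work together in the combined arm. Judging adherence, and dissuading a patient from continuing, both involve discretion. The article does not say who decides on exclusion under 2.5.2.

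Both primary outcomes are at stake. A woman excluded under 2.5.2 loses her BMD change and her response category together. If her week-12 scan was never taken, no later analysis rule can recover it.

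**Working it through.** **Inputs from the article**
- Sample size (2.8): 87 required, 10% loss, 96 in total, 32 per arm.
- Sessions: CEA 12 (2.9.2); rTMS 5 × 4 + 2 × 8 = 36 (2.9.3); combined 12 + 36 = 48 (2.9.4).
- Post-baseline DXA scans: one, at week 12 (2.10.1, Table 1).

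**The planned allowance.** 87 × 1.10 = 95.7, rounded up to 96, reproduces the stated total (87 / 0.90 = 96.7 would give 97). The allowance is 96 − 87 = 9 women, or 3 per arm, and it must also cover withdrawal and true loss. Nothing limits exclusions under 2.5.2 b and c to this number.

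**Inputs that must be assumed.** The article gives no rate of treatment stopping or exclusion, no response rate and no SD for BMD change. All that follows is illustration, with loss from one arm and none elsewhere.

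**BMD change.** If k of 32 women are removed and the retained differ from the removed by d, the arm mean shifts by (k/32) × d.
- k = 1, d = 0.5 SD: (1/32) × 0.5 = 0.016 SD
- k = 3, d = 1 SD: (3/32) × 1 = 0.094 SD

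**Effective rate**, assumed truly 16/32 = 50.0%, with the removed women left out of the calculation:

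| Removed | all non-responders | all responders |
|---|---|---|
| 1 | 16/31 = 51.6% | 15/31 = 48.4% |
| 2 | 16/30 = 53.3% | 14/30 = 46.7% |
| 3 | 16/29 = 55.2% | 13/29 = 44.8% |

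The largest shift is 5.2 points in either direction.

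**Scale.** The standard error of a two-arm difference at 32 per arm is √(2/32) = 0.25 SD for BMD change and √(0.25 × 2/32) = 12.5 points for the rate. At 1 to 3 losses the shift is smaller than chance error.

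**A second illustration, allowing more removal.** Suppose removal depends on an index that has correlation r with a normally distributed outcome, and a fraction q of one arm is removed from the low end. The retained mean then shifts by r × φ(z) / (1 − q), where z is the normal quantile at q and φ the normal density.
- q = 10%: 0.04 SD at r = 0.2; 0.19 SD at r = 1 (the worst tenth removed)
- q = 20%: 0.07 SD at r = 0.2; 0.35 SD at r = 1

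Only the extreme case at 20% exceeds the standard error of 0.25 SD. A larger sample would reduce the standard error but not the shift.

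**The case against.** The strongest reply is that the article does not say what is read into it. Section 2.5.2 does not state that women are excluded from the analysis. Section 2.5 speaks of categorising non-completers, so 2.5.2 could be a label or the seed of a per-protocol set. This is a journal article, and analysis sets are commonly left to the full protocol or the SAP. In part this stands: the wording is ambiguous. But the concern is with a rule that is written down. A list of exclusion criteria for enrolled women is most plainly read as removing them, and neither 2.14 nor any other section says otherwise.

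A reader might go further and infer that 2.5.1 and 2.5.4 take women who stop treatment out of the trial and cancel their week-12 scan. The text does not support that. Neither section says that visits end. Item a of 2.5.4 speaks of continuing treatment, while item d separately names withdrawal from the study. Table 1 schedules the week-12 DXA without exception, and 2.12 aims to limit missing data. What remains is that the two kinds of stopping share one list, and that no sentence asks a woman who has stopped to attend. Section 2.11.2 also ties the second blood sample to the end of treatment, which for her is not week 12.

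A reader might also treat the undefined denominator in 2.10.2, or the counting of missing scans, as part of the fault. Those are details commonly left to the SAP and are not raised here.

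Finally, different session counts do not prove different loss, and the illustrated shifts are mostly small. Both objections stand and limit how firmly the point can be put.

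**Conclusion.** The point holds for 2.5.2 b and c. Followed as written, they make both primary comparisons depend on adherence and record completeness after randomisation, and nothing in the article keeps the excluded women's data. Sections 2.5.1 and 2.5.4 add to the risk without being wrong in themselves.

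Bias is possible, not established, and its direction is unknown. Within the planned allowance of 3 per arm it would be about 0.02 to 0.09 SD, or up to 5.2 points, on the assumed differences and one-sided loss; both figures are below the standard error. It matters more if exclusions exceed the allowance, which the text does not prevent. The case for acting rests on the low cost of the remedy and on the fact that an untaken scan cannot be recovered, not on a demonstrated large effect.

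**What to change.** - **2.5.2 and 2.14:** state that the primary analysis includes all randomised participants as assigned, and that 2.5.2 b and c define only a per-protocol sensitivity analysis.
- **2.5.1 and 2.5.4 (a, b, c, e):** separate stopping study treatment from leaving the study. State that women who only stop treatment are still asked to attend for the scheduled week-12 DXA, blood sample and scales, timed from randomisation, where medically feasible and unless consent is withdrawn. Record the date treatment stopped.

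The cost is a short amendment, with ethics review, in a trial that is already recruiting (2.16), and the effort of recalling a few women. For those with a severe reaction or serious illness the scan may not be feasible, hence the qualification. No assessment is added, because the week-12 measurements are already scheduled for everyone.

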#### Exclusion criteria

2.5.2

a Those who do not meet the inclusion criteria and are mistakenly included;

b Subjects with poor adherence, not following the designed treatment regimen strictly, or whose something would affect the observed results of the study during the trial;

c Subjects with incomplete information on various materials.

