### Statistical analysis

2.14

The data will be recorded and checked for accuracy, and the data related to baseline and clinical symptoms will be statistically analyzed using SPSS 27.0 software. The *t*-test will be performed for customarily distributed measures that meet the chi-squared test, and the *t′*test will be conducted for standards that meet the normal distribution but do not meet the chi-squared test. Independent sample *t*-tests are used between two groups, and paired sample *t*-tests will be used for pre-treatment and post-treatment comparisons within groups. Non-normally distributed measures are described by “median (interquartile range)” [*M (IQR)*], and non-parametric tests will be performed. *The Mann–Whitney U* test will compare two independent samples, and the *Wilcoxon Z* test will be used for pre-and post-treatment-comparisons. The scale scores at more than three of these time points are compared using repeated measures *ANOVA*. Correlations will be expressed as correlation coefficients (*r*). Correlations between the two measurement variables will be analyzed by Pearson correlation analysis if they conform to a normal distribution and Spearman analysis if they do not obey a normal distribution. Given that our study defines two primary outcomes, a Bonferroni correction will be applied, thus adjusting the significance level for individual outcome analyzes to *α*/2 to control the overall type I error rate, setting *α* = 0.05 (39).

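### Section 2.5.2 excludes randomised patients for poor adherence, incomplete information or anything affecting the results, which can bias every between-arm comparison in either direction

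*Protocol article*

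**What the plan says.** Section 2.5 deals with people already in the trial: "For those who did not complete the trial within 12 weeks±5 days, categorization will be made according to the reason for not completing the trial". It then sets out separate lists.

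- Section 2.5.1 (drop-out) covers withdrawal by the patient or on the doctor's advice: "Including patient self-withdrawal due to poor efficacy, intolerance" and further reasons, including poor adherence.
- Section 2.5.2 (exclusion criteria) has three items. Item (a) covers ineligible patients entered in error. Item (b) reads "Subjects with poor adherence, not following the designed treatment regimen strictly, or whose something would affect the observed results of the study", limited to the trial period. Item (c), on gaps in the records, reads "Subjects with incomplete information on various materials".
- Section 2.5.4 (discontinuation) again includes poor compliance.

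Exclusions at entry stand elsewhere, in section 2.4. Section 2.14 (statistical analysis) does not refer to any of these categories and does not say that the patients in them stay in the comparison. Section 2.8 allows one overall attrition rate of 10%, with no rate by arm.

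**The concern.** Items (b) and (c) of section 2.5.2 depend on what happens after allocation. Whether a patient keeps strictly to the regimen, or has complete records, can depend on which treatment she was given and how she is doing on it. Removing patients on those grounds gives up the protection of randomisation in every between-arm comparison, including both primary outcomes.

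Three features make the rule worse than an ordinary per-protocol definition:

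- **The clause on anything affecting the results is open-ended.** It does not say what qualifies, who decides or by when, so a patient could be removed once her outcome is known.
- **The judgement is unlikely to be blind.** The therapists in section 2.7 deliver the treatment, know the arm, and are best placed to judge adherence.
- **The categories overlap.** Poor adherence is in sections 2.5.1, 2.5.2 and 2.5.4, so the same patient can be a drop-out, an exclusion or a discontinuation at discretion.

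**Working it through.** **What section 2.5.2 is for.** Entry exclusions are in 2.4, drop-outs in 2.5.1 and discontinuation in 2.5.4. What is left for 2.5.2 is removal of the patient's data. Item (c) makes little sense otherwise, because incomplete records are not a reason to stop treating someone.

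**Treatment load by arm (2.9.2 to 2.9.4).** CEA: 12 weekly sessions. rTMS: 5 × 4 + 2 × 8 = 36, which matches the stated total. Combined: 12 + 36 = 48 administrations. These need not be 48 visits, since the text does not say whether CEA and rTMS fall on the same day.

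**Possible size.** The documents give 32 patients per arm. The exclusion fractions d and the correlation r between adherence and outcome are assumptions. Suppose there is no true effect and the least adherent fraction d of an arm is removed. The mean of those retained then shifts by

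r × φ(z_d) / (1 − d), in SD units, where z_d is the d-quantile of the standard normal.

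The multiplier of r is:

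- d = 5%: 0.1031 / 0.95 = 0.109
- d = 10%: 0.1755 / 0.90 = 0.195
- d = 20%: 0.2800 / 0.80 = 0.350
- d = 30%: 0.3477 / 0.70 = 0.497

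The bias is r times the difference between the multipliers of the two arms. Type I error comes from a two-sided z test with SE = √(1/[32(1 − d₁)] + 1/[32(1 − d₂)]), taking the SD as unchanged by the removal.

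| Excluded, combined v comparator | Bias (SD), r = 0.2 / 0.3 / 0.5 | Type I error at 0.05, r = 0.2 / 0.3 / 0.5 |
|---|---|---|
| 10% v 10% | 0 / 0 / 0 | 0.050 / 0.050 / 0.050 |
| 20% v 10% | 0.031 / 0.046 / 0.077 | 0.051 / 0.053 / 0.059 |
| 20% v 5% | 0.048 / 0.072 / 0.121 | 0.054 / 0.058 / 0.073 |
| 30% v 10% | 0.060 / 0.091 / 0.151 | 0.055 / 0.062 / 0.083 |

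Example, 30% v 10% with r = 0.5. The bias is 0.5 × (0.497 − 0.195) = 0.151. The SE is √(1/22.4 + 1/28.8) = 0.282, and the ratio is 0.151 / 0.282 = 0.536. Type I error is Φ(−1.96 + 0.536) + Φ(−1.96 − 0.536) = 0.077 + 0.006 = 0.083.

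At the Bonferroni level of 0.025 in section 2.14, the unequal rows give 0.026 to 0.047. The more extreme pairing of 30% v 5% lies outside the table. At r = 0.5 it gives 0.248 − 0.054 = 0.194 SD and a type I error of 0.107 at 0.05. If r is negative, so that the excluded patients would have done better, the sign of every entry reverses.

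**The case against.** **Removal from the analysis is not stated in words.** Section 2.5 speaks only of categorising non-completers, and section 2.14 never mentions the categories. A reader might infer that the protocol prescribes a completers' analysis and nothing else, or that the 10% attrition allowance proves it. The text does not go that far: inflating a sample size for attrition is routine. Analysis sets may also be defined in a SAP that is not shown, so their absence is not the defect. What stands is the wording of 2.5.2. A later intention-to-treat definition would contradict it, so it needs amending in any case.

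**The direction is not established.** It is tempting to say that the rule favours the combined arm because its treatment load is highest. That needs more exclusions in that arm and worse outcomes among those excluded. The load makes this plausible, but the documents give no rate by arm.

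**Comparison with the pilot data can mislead.** A bias of 0.15 SD looks like twice the pilot difference between combined and CEA, 0.17 / √((2.17² + 2.84²)/2) = 0.07 SD. Against rTMS the pilot difference is 0.99 / √((2.17² + 1.77²)/2) = 0.50 SD. Both concern the SF-MPQ, which the text of sections 2.9.1 and 2.11 treats as secondary. The ratio shows little.

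**Repeated-measures ANOVA is a side issue.** Section 2.14 says "The scale scores at more than three of these time points are compared using repeated measures" ANOVA. Complete-case use could lose 10% to 23% of patients (1 − 0.98⁵ to 1 − 0.95⁵) if 2% to 5% were missing independently at each of five post-baseline visits. If the same patients miss every visit the loss is only 2% to 5%. BMD and total efficiency are measured only at weeks 0 and 12, so the method does not touch them.

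**There is some blinding.** Section 2.7 keeps allocation from the evaluator and gives the statisticians only group codes. That lowers the risk of selective removal but does not bind whoever applies the exclusions.

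**Conclusion.** The point holds. It concerns a rule that the protocol fixes badly, not a detail left out. Following section 2.5.2 on its natural reading means comparing groups that are no longer those randomised, and the open-ended clause permits removal with outcomes in view. The bias can run in either direction, with the combined arm possibly the most affected.

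The size cannot be derived from the documents. For the three unequal pairings in the table it is about 0.03 to 0.15 SD, with type I error of 0.051 to 0.083 against 0.05. It is zero when exclusion is equal under the same mechanism and larger if exclusion is more unequal. The case for change rests on the rule and not on any one of these figures. It should be corrected before analysis because it reaches both primary outcomes.

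**What to change.** 1. State that the primary analysis includes all randomised patients in their assigned arm.
2. Keep collecting outcomes at the visits already scheduled from patients who stop treatment, unless they withdraw from the study.
3. Delete the clause on anything that would affect the observed results.
4. Use the remaining criteria of 2.5.2 only to define a per-protocol sensitivity set, with membership fixed before the group codes are broken.
5. As a companion change for the scales measured at six time points, use a mixed model that keeps patients with a missed visit. The missing-data method for the primary outcomes can be left to the SAP.

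The cost is mainly wording, plus some effort to follow up patients who have stopped treatment. Estimated effects may come out smaller than in a completers' analysis.

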#### The CEA group

2.9.2

Our treatment method is based on previous literature reports (30).

The treatment group will undergo 12 weekly sessions of CEA for 3 months. The primary acupoints will be BL23, SP6, and RN4, with additional acupoints like BLI8, GB39, BL11, BL20, and ST36 added, depending on whether the case is a liver-kidney deficiency or kidney yang deficiency. During each treatment, RN4 is essential, while the other acupoints can be alternated between the left and right sides. The acupoint location method will follow the State Bureau of Technology Supervision standards. In addition, the operating procedure will be based on the National Standards of GB/T 21709.10–2008 manipulations of acupuncture and moxibustion, Part 10 Acupoint catgut embedding. Detailed information about the intervention group and acupoint location can be found in Tables 2, 3 of the STRICT checklist for reporting interventions in clinical acupuncture trials (Tables 2, 3).

**Table 2 tab2:** Acupoints selection.

Primary point	Additional point	
	Deficiency of liver and kidney	Deficiency of kidney yin
Shenshu (BL23) Sanyinjiao (SP6) Guanyuan (RN4)	Dazhu (BL11) Ganshu (BL18)	Xuanzhong (GB39) Zusanli (ST36) Pishu (BL20)

**Table 3 tab3:** Acupoints location.

Point	Location
BL23	1.5 cun lateral to the depression below the spinous process of the second lumbar vertebra
SP6	Posterior to the mesial border of the tibia and 3 cun above the tip of the medial malleolus
RN4	On the anterior midline, 3 cun below the umbilicus
BL18	1.5 cun lateral to the depression below the spinous process of the 9th thoracic vertebra
BL11	1.5 cun lateral to the lower border of the spinous process of the first thoracic vertebra
GB39	3 cun above the tip of the external malleolus, on the anterior border of the fibula
ST36	3 cun directly below Dubi (the lateral depression of the knee-joint) and one middle finger-breadth lateral to the anterior border of the tibia
BL20	1.5 cun lateral to the depression below the spinous process of the 11th thoracic vertebra

Cun=an acupuncture measurement unit; 1 cun corresponds to the study subject’s thumb width.

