#### The rTMS group

2.9.3

The treatment will be completed by a trained professional therapist using a transcranial magnetic stimulator (YRD CCY-II from Wuhan Eredo). The motor threshold (MT) and dorsolateral frontal lobe (DLPFC) stimulation site are to be determined during the first treatment. The room temperature will be maintained at 16°C–23°C, and the patient will be lying flat on their side on the treatment bed. The motor-evoked potentials (MEPs) are to be recorded in the contralateral hand’s interosseous muscle through the magnetic stimulator’s electromyographic amplifier, with the center of the “8” coil placed on the right temporal cortex of the subject. The stimulation site and the stimulation volume are adjusted until at least 5 out of 10 stimulations evoke MEPs with an amplitude more significant than 50 μV, at which point the magnetic flux is MT, and move 4 cm forward horizontally at the site where the MEPs are elicited, which is the DLPFC. We plan to utilize a positioning cap and a transcranial magnetic stimulator (YRD CCY-II from Wuhan Iredell) to accurately identify and target the specific location during the procedure (31). We intend to choose the right DLPFC point as the stimulation site. The stimulation intensity will be set at 80% of the resting movement threshold, with a frequency of 1 Hz, lasting 30s with an interval of 4 s, and 10 series to be performed continuously on the patient (32, 33). The treatment plan will consist of one session per day, 5 days a week, for 4 weeks (34, 35). Starting from the fifth week, the treatment plan changes to twice a week for eight consecutive weeks (36). In total, this treatment plan will last for 12 weeks and include 36 sessions.

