#### The CEA combined with rTMS group

2.9.4

Subjects in this group will receive both the CEA and the rTMS treatment according to the respective regimens of the two therapies.

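### Section 2.5.2b excludes already randomised women for poor adherence or an unspecified influence on results; they should stop treatment at most, and stay in follow-up and in their arm

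*Protocol article*

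**What the plan says.** Entry exclusions are in section 2.4. Section 2.5 opens by saying that, for women who do not complete the trial within 12 weeks ± 5 days, "categorization will be made according to the reason for not completing the trial". Four subsections follow. Three of them matter here.

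- **2.5.1, drop-out**, includes "doctor dissuasion due to poor adherence".
- **2.5.2, a second list of exclusion criteria**, includes as item b: "Subjects with poor adherence, not following the designed treatment regimen strictly, or whose something would affect the observed results of the study". The item ends by placing these events within the trial period. Item a of the same list covers women enrolled by mistake.
- **2.5.4, discontinuation**, includes as item c "Subjects who have poor compliance and do not cooperate with the relevant treatment despite repeated explanations" and as item e "Subjects who take other drugs privately during the treatment period, which may interfere with the study results". Items a and c of that list concern treatment; items d and f concern withdrawal from the study and loss to follow-up.

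The treatment loads are stated in section 2.9. For CEA: "The treatment group will undergo 12 weekly sessions of CEA for 3 months". For rTMS: "In total, this treatment plan will last for 12 weeks and include 36 sessions". For the combined arm: "Subjects in this group will receive both the CEA and the rTMS treatment according to the respective regimens of the two therapies".

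Section 2.7 blinds the evaluator and the statisticians through group codes. The therapists deliver the treatment and so know it.

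**The concern.** A randomised comparison is protected only while the women compared are those who were randomised. Adherence, strict observance of the regimen, drug use and any other influence on results are all observed after randomisation, and each can depend on how the woman is doing. Taking an analgesic because pain is poorly controlled would be one example; that is my inference, since the document does not mention analgesics.

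If such women are removed, and if removal differs between arms in number or in its relation to outcome, the remaining groups are no longer comparable. The outcomes exposed are those that pain, mood or symptoms can move: SF-MPQ, OSS, BDI-II and the pain part of *Effective* in section 2.10.2, which feeds a primary outcome. The open-ended last clause of 2.5.2b adds to this, because it could justify removing almost anyone. If the rules also end a woman's visits, the missing scores cannot be recovered later, whatever analysis set is chosen.

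**Working it through.** **1. Does the rule reach randomised women?** Yes. Section 2.4 already holds the entry exclusions. Section 2.5.2 is a separate list, its item a concerns women who are already in, and item b refers to events during the trial. Nothing in section 2.14 overrides it. Section 2.5.4e is less clear: its list mixes stopping treatment (a, c) with leaving the study (d, f), so item e can be read either way.

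**2. Can removal differ by arm?** Treatment loads from section 2.9:
- CEA: 12
- rTMS: 5 × 4 + 2 × 8 = 36, which agrees with the stated total
- combined: 12 + 36 = 48 treatments (36 attendances if each CEA session shares a visit with an rTMS session)

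**3. Illustration of how the wording of the adherence rule matters.** Assume that each session is missed independently at the same rate *p* in every arm. These figures are not expected losses.
- If strict adherence means no missed session, the share affected is 1 − (1 − p)^n.
- If the rule means more than 20% of sessions missed, the counts are at least 3 of 12, 8 of 36 and 10 of 48 (binomial).

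| Reading | p | CEA | rTMS | Combined (48) |
|---|---|---|---|---|
| Any session missed | 0.5% | 5.8% | 16.5% | 21.4% |
| Any session missed | 1% | 11.4% | 30.4% | 38.3% |
| More than 20% missed | 10% | 11.1% | 2.4% | 1.9% |

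The order of the arms reverses between the readings. With shared visits, the combined arm would have the rTMS figure in the first two rows.

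**4. Illustration of the effect on SF-MPQ.** The pilot SDs in section 2.8 are 2.84, 1.77 and 2.17. Pooled SD = √((2.84² + 1.77² + 2.17²)/3) = √((8.07 + 3.13 + 4.71)/3) = 2.30 points.

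If a fraction f of an arm is removed and the removed women differ from their arm mean by d SD, the mean of those remaining shifts by d × f/(1 − f). The bias in a two-arm difference, with the same d in both arms, is d × [f₂/(1 − f₂) − f₁/(1 − f₁)].

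With assumed f₁ = 0.05 and f₂ = 0.15, the bracket is 0.1765 − 0.0526 = 0.124.

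| d (assumed) | Bias, SD | Bias, points |
|---|---|---|
| 0.25 | 0.031 | 0.07 |
| 0.5 | 0.062 | 0.14 |
| 1.0 | 0.124 | 0.29 |

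With f₁ = f₂ and the same d, the bias is 0.

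**5. Scale.** The differences between the pilot mean changes are 17.40 − 17.23 = 0.17 points (combined versus CEA) and 17.40 − 16.41 = 0.99 points (combined versus rTMS). With 29 women per arm (87/3), the standard error of a two-arm difference is 2.30 × √(2/29) = 0.60 points.

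**The case against.** Several counter-arguments have force.

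- **The lead-in limits the section.** Section 2.5 sorts women who did not complete within the window. A woman who misses one session but finishes on time may never come under 2.5.2b. This stands. A reader might infer from the table that up to 38% of the combined arm would be lost; the document does not support that.
- **Visits may be shared.** Section 2.7 has two physicians working together on the combined arm, and nothing puts CEA and rTMS on separate days. This stands. The modelled gap between combined and rTMS could vanish, though the gap between CEA and the other two would not.
- **Everything about size is assumed.** Miss rates, removal fractions and outcome differences are my inputs, and the largest illustrated bias (0.29 points) is about half the standard error of 0.60. This stands as to size; it does not make the rule a sound one.
- **Loss of data is inferred.** A reader might infer that excluded women's assessments stop or that their data are discarded. The document says neither, and analysis sets are commonly left to the statistical analysis plan, which is not shown. But exclusion of enrolled women is a rule the document does state, and removal is its natural reading.
- **Some gaps are ordinary condensation.** The missing adherence threshold, the absence of a list of interfering drugs (section 2.5.3 already prohibits anti-osteoporosis drugs) and the question of who applies the rules can sit in the full protocol. Poor adherence appears under three headings, but no different handling is attached to them, so that overlap is minor. None of these is pressed here.

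**Conclusion.** The point holds as a risk created by a stated rule. Section 2.5.2b, followed as written, excludes randomised women on post-randomisation grounds that may relate to outcome, one of them open-ended; 2.5.4e can be read the same way. Unequal treatment loads and therapists who know the treatment make removal that differs by arm plausible, but the document does not show that it will occur.

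Direction and size cannot be computed from the document. The 0.07 to 0.29 SF-MPQ points rest on assumed removal of 5% versus 15% and on removed women lying 0.25 to 1.0 SD from their arm mean. No bias is claimed for BMD or for the *Significant efficacy* category, and a reader should not extend the point to them. Because the harm is conditional and the correction is small, I class this as a cheap improvement.

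**What to change.** In section 2.5:

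1. State that poor adherence or taking an interfering drug may stop study treatment but does not remove the woman from the trial. She keeps every scheduled assessment, including both follow-up visits, and is analysed in her randomised arm.
2. Delete the open-ended last clause of 2.5.2b as a ground for exclusion.
3. In 2.5.4, separate stopping treatment (a, b, c, e) from leaving the study (d, f).
4. Confine any adherence-based exclusion to a per-protocol sensitivity analysis.

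The cost is a few sentences, plus keeping the affected women in visits already on the schedule. Section 2.16 says recruitment is under way, so the change is worth making soon. The downside is that observed scores will include some effects of non-adherence or of other drugs. Recording concomitant drug use by arm, with a sensitivity analysis for the scores it may affect, addresses this. Which drugs are clinically acceptable remains for the investigators to decide.
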